### 6.4 Handling of FDG and FLT safety

No adverse events were described after administration of FLT and FDG up to now. In any case of adverse event, especially allergic reaction, the next dose of FLT or FDG, respectively, will not be administered.

## **7 STATISTICS**

### **7.1 Statistical formulation of study objectives and design**

#### **Primary Objective**

To evaluate the accuracy of FDG-/FLT-PET analyses for early prediction of non-progression in patients with NSCLC treated with erlotinib

#### **Secondary objectives**

1. To identify PET characteristics for progressive disease following erlotinib treatment
2. To identify PET characteristics for response to erlotinib
3. To identify PET characteristics for stable disease following erlotinib treatment
4. To confirm the statistical association of EGFR mutational status and clinical response in NSCLC patients treated with erlotinib
5. To confirm the statistical association of KRAS mutational status and clinical resistance to treatment of NSCLC patients with erlotinib
6. To determine the discriminatory capability of FDG-/FLT-PET regarding EGFR and KRAS mutational status in NSCLC patients
7. To compare prognostic value of FDG-PET, FLT-PET and EGFR mutational status regarding clinical response in NSCLC patients treated with erlotinib
8. To identify EGFR and KRAS sequence characteristics for clinical response and stable disease following erlotinib treatment
9. To assess safety of erlotinib
10. To determine response rates
11. To determine rates of stable diseases
12. To determine one-year FFTF
13. To determine one-year OS
14. To determine median overall survival time

#### **Endpoint**

##### **Primary endpoint**

Non-progression to therapy with erlotinib, FLT and FDG standard uptake values

##### **Secondary endpoints**

FLT and FDG standard uptake value, EGFR mutational status, KRAS mutational status, EGFR positivity in immunohistochemistry, safety

One year FFTF, one year OS

#### **Definitions and explanations**

Response criteria are according to the Response Evaluation Criteria in Solid Tumors (RECIST) (<http://www3.cancer.gov/bip/RECIST.htm>)

### **Evaluation of target lesions**

- \* Complete Response (CR): Disappearance of all target lesions
- \* Partial Response (PR): At least a 30% decrease in the sum of the longest diameter (LD) of target lesions, taking as reference the baseline sum LD
- \* Progressive Disease (PD): At least a 20% increase in the sum of the LD of target lesions, taking as reference the smallest sum LD recorded since the treatment started or the appearance of one or more new lesions
- \* Stable Disease (SD): Neither sufficient shrinkage to qualify for PR nor sufficient increase to qualify for PD, taking as reference the smallest sum LD since the treatment started
- \* Non-progression: CR + PR + SD but not PD

### **Hypotheses, clinical**

1. A difference in early FDG- or FLT-PET examinations between progressers (PD) and non-progressers (CR, PR, SD) in NSCLC patients treated with erlotinib can be detected.
2. EGFR mutations are found in patients with CR or PR and KRAS mutations in patients with PD after treatment with erlotinib.

### **Trial design**

The trial will be performed as a single-arm, single-center, open-label study.

### **Recruitment**

Patients will be recruited after screening only if all inclusion criteria are met, no exclusion criteria are met and written informed consent has been obtained.

### **Cancellation of recruitment**

The recruitment of patients who are not qualified for the trial can be cancelled. Evidence that the patient is not qualified must be based on data obtained before inclusion (e.g., histology, staging, case history or previous treatment). Only for those patients who were recruited in error without knowledge of these data recruitment can be cancelled. Those for whom a physician later assesses the findings differently or discovers additional involved sites over the course of time (e.g. because of delays in treatment) cannot be cancelled.

## **7.2 Analysis and trial termination strategy**

### **Interim analyses**

No interim analysis is planned.

## Early stopping strategy

The trial will be stopped early if unexpectedly high rates of SAEs are observed.

## Analyses of primary endpoints

1. The prognostic value/accuracy of FDG-/FLT-PET regarding non-progression in NSCLC patients treated with erlotinib will be evaluated by ROC analysis (area under the ROC curve, AUC);  $H_0: AUC_{\text{FDG/FLT PET}} \leq 0.5$ ,  $H_A: AUC_{\text{FDG/FLT PET}} > 0.5$  (intersection-union test at one-sided level 2.5% – *primary objective*).

2. The statistical association of EGFR respectively KRAS mutational status, EGFR positivity and clinical response in NSCLC patients treated with erlotinib will be evaluated by Fisher's exact test (at one-sided level 2.5%; strong type 1 error control is maintained if analysis of item 1 was significant – *secondary objective*).

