#### **1.4 FDG- and FLT-PET for assessment of response to treatment**

The addition of FDG (fluoro-deoxy-glucose)-PET to conventional pre-treatment workup has now become part of the guidelines of the American Society of Clinical Oncology (ASCO) for the diagnostics of patients with lung cancer (Pfister et al., 2004). This is due to an increase in specificity and sensitivity as compared to conventional CT scans (Pieterman et al., 2000; van Tinteren et al., 2002). In addition, substantial progress in measurement of tumor cell proliferation by PET has been made by synthesis of FLT (fluoro-L-thymidine, (Shields et al., 1998). FLT is trapped in tissue after phosphorylation by thymidine kinase 1 (TK1), resulting in high accumulation in tumors compared to non malignant tissue. In NSCLC, a high correlation was found between standardized uptake value (SUV) measures of FLT uptake and Ki-67 scores, an established marker of tumor cell proliferation (Buck et al., 2003; Buck et al., 2002). In these studies, the specificity was 100% and the sensitivity was ~85%. These findings suggest FLT-PET to become an ideal complementary technology to FDG-PET due to its higher specificity. Here, we hypothesize that a decrease in tumor cell proliferation as an early event during the response to erlotinib may be visualized by FDG- and/or FLT-PET and, vice versa, absence of this response may predict early progress. This hypothesis is mainly built on the following findings: Tumor cell proliferation was rapidly reduced by erlotinib in an in-vitro model of lung adenocarcinoma (Pao et al., 2004). Since at least FLT-PET was shown to directly correlate to tumor cell proliferation (Buck et al., 2003; Buck et al., 2002), we assume that FDG-/FLT-PET will allow to early determine response status of a patient under erlotinib treatment. Further clinical and experimental data support our hypothesis: In several early clinical studies it has been demonstrated for different malignancies such as breast cancer (Rousseau, 2005), soft tissue sarcoma (Schuetze, 2005), glioblastoma (Charnley NG, 2005), rectum cancer (Di Fabio, 2005) and lung cancer (Griesinger, 2005; Schmuecking,

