## Sample size calculation

Assumptions:

- (1) 10% responder, 60% progressers; thus 40% non-progressers
- (2) Primary variable is the 'area under the ROC curve (AUC,  $\vartheta$ )', (PET-values of non-progressers > progressers)
- (3) Variability in the PET-results of non-progressers is greater than that of progressers
- (4) Type-I-error 0.05; type-II-error 0.20
- (5) True accuracy (AUC) is at least 0.70 (alternative hypothesis; some common diagnostic tests have an AUC greater than 0.70 [1; p29])

Sample size calculation:

| AUC ( $\vartheta$ ) | # Non-progressers | # progressers | # Total   |
|---------------------|-------------------|---------------|-----------|
| 0.70                | 26                | 38            | 64        |
| 0.75         | 16         | 24     | 40 |
| 0.80                | 11                | 16            | 27        |

Note: The sample size was calculated using formulae (6.3) and (6.6) in [Zhou et al., 2002; p199, 201].

Thus, assuming  $\vartheta_1 = 0.75$ , 40 patients are needed to reject the null hypothesis  $H_0: \vartheta = 0.5$  in favour of the alternative  $H_1: \vartheta \neq 0.5$ . The sample size will be sufficient to yield a 95% confidence interval for  $\vartheta$  with width  $2 \times 0.17 = 0.34$ .

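### The primary intersection-union test needs both tracers to succeed, but N=40 was sized for one AUC and hypothesis 1 needs only one tracer: joint power is about 64–75%, not 80%

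*Protocol*

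**What the plan says.** Section 7.2, Analyses of primary endpoints, evaluates FDG-/FLT-PET by ROC analysis with an "intersection-union test at one-sided level 2.5" percent. The null is written with the single symbol AUC for FDG/FLT PET. Item 2 of that section adds Fisher tests of mutational status, EGFR positivity and response, with strong type 1 error control if item 1 was significant.

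Section 7.1, Hypotheses, clinical, begins hypothesis 1 with "A difference in early FDG- or FLT-PET examinations between progressers (PD) and non-progressers (CR, PR, SD", the difference being one that can be detected. Section 1.4 expects that reduced proliferation "may be visualized by FDG- and/or FLT-PET". The primary objective in 7.1 says only FDG-/FLT-PET.

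Section 7.3, Sample size calculation, names one parameter ("Primary variable is the 'area under the ROC curve (AUC") and sets "Type-I-error 0.05; type-II-error 0.20", "10% responder, 60% progressers; thus 40% non-progressers" and "True accuracy (AUC) is at least 0.70". It concludes that "40 patients are needed to reject the null hypothesis" at an AUC of 0.75. It mentions no second tracer, no joint power and no correlation between tracers. Section 7.4 plans a nonparametric ROC analysis by DeLong's method.

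**The concern.** An intersection-union test rejects only when every component null is rejected, here each at the full 2.5%. The probability that two tests both succeed cannot exceed the power of the weaker one, and equals the single-tracer power only if the two always succeed or fail together. A sample size that gives 80% for one AUC therefore gives less for the pair.

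Hypothesis 1, by contrast, is already true if a single tracer discriminates. So a trial could bear out hypothesis 1 and still miss its primary criterion. The Fisher tests in item 2 would then lose the error control that depends on item 1. The test, the hypothesis and the sample size are all fixed in the protocol itself, and as written they do not fit together.

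**Working it through.** **Inputs.** From 7.3: AUC 0.75 against 0.5, type-I error 0.05 with a two-sided alternative (z = 1.96), power 80% (z = 0.8416), 40:60 split, so R = 1.5 progressers per non-progresser. From 7.2: one-sided 2.5%, which has the same critical value of 1.96. Assumed: the correlation between the FDG and FLT test statistics, shown from 0 to 0.9. The cited textbook formulae are not at hand; the usual binormal one-AUC variance was used and is supported by its match to the protocol's table.

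**Reproducing N.**

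V(A) = 0.0099·exp(−a²/2)·[(5a² + 8) + (a² + 8)/R], with a = 1.414·Φ⁻¹(A)

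V(0.5) = 0.0099 × (8 + 8/1.5) = 0.1320. For A = 0.75, a = 0.9537 and V = 0.1162.

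n = [1.96·√0.1320 + 0.8416·√0.1162]² / 0.25² = 15.97 non-progressers; × 1.5 = 23.95 progressers.

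This is the protocol's 16 + 24 = 40. The same formula gives 25.41 and 38.11 at AUC 0.70 (protocol 26 and 38), and 10.75 and 16.13 at 0.80 (protocol 11 and 16). A one-sided 0.05 test would give a total of 32, so 1.96 was the value used.

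**Power for one tracer at N = 40.**

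Φ([0.25·√16 − 1.96·√0.1320] / √0.1162) = Φ(0.845) = 80.1%. The same formula gives 59.9% at AUC 0.70 and 93.5% at 0.80.

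**Power for both tracers, planning formula.** At correlation 0 this is the product, e.g. 0.801² = 0.641; otherwise the bivariate normal probability.

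| Correlation of test statistics | Both AUC 0.75 | AUC 0.75 and 0.70 | Both AUC 0.80 |
|---|---|---|---|
| 0 | 64% | 48% | 87% |
| 0.5 | 69% | 54% | 89% |
| 0.9 | 75% | 59% | 91% |

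With both AUCs at 0.75 the figure reaches 80% only at correlation 1. Over this range the type-II error is 25–36% instead of 20%.

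**Check with the planned analysis.** The DeLong test was simulated with 16 against 24 normally distributed marker values at AUC 0.75. It gives about 83% for one tracer, and 68%, 72% and 78% for both at marker correlations 0, 0.5 and 0.9.

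**Worst case: one tracer at AUC 0.75, the other at 0.50.** At independence, 0.801 × 0.025 = 2.0%. The DeLong simulation gives 2.9% at marker correlation 0.5.

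**Holm on the two tracers at N = 40, DeLong simulation.** At least one tracer is found in 94%, 89% and 82% of trials at marker correlations 0, 0.5 and 0.9 when both AUCs are 0.75, and in about 76% in the worst case above.

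**The case against.** Requiring both tracers is a legitimate, stricter choice and does not inflate the type I error. The trial is a single-arm exploratory phase II study, and each AUC can be reported whatever the formal result. The power loss depends on a correlation that nobody has stated, and at an AUC of 0.80, a row of the protocol's own table, joint power exceeds 80% throughout. All of this stands and limits the size of the point, but none of it makes the stated 80% the power of the stated test at the design AUC.

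Three stronger readings are tempting and not supported:

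- *The trial tests the wrong claim.* The objective's FDG-/FLT-PET does not settle both versus either, and section 1.4 allows *and* as well as *or*. Only hypothesis 1 says *or*. The documents show an inconsistency, not which side of it is mistaken.
- *Failing item 1 bars the Fisher tests.* Item 2 ties only strong type 1 error control to item 1, and the secondary analyses plan Fisher's test again. Confirmatory status is lost; the tests can still be run.
- *The 2–3% figure is what to expect.* It needs one tracer at exactly 0.50, whereas 7.3 assumes a true accuracy of at least 0.70. Section 1.4 cites an animal model in which FLT outperformed FDG, which suggests unequal tracers, not a useless one.

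**Conclusion.** The point holds. At the design AUC of 0.75 for both tracers, the primary test has about 64–75% power by the protocol's planning approach, or about 68–78% for the DeLong analysis, against the 80% implied by 7.3. The ranges rest on assumed correlations of 0 to 0.9 and on exactly 16 and 24 evaluable patients. At 0.80 for both, planning-formula power is 87–91%.

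A reader might add up two failures, too little power and the wrong test, but these belong to alternative readings. If both tracers are meant to succeed, the stated power is wrong and the procedure is right. If either is enough, the procedure is wrong, and N = 40 is roughly adequate with an adjusted test. Under each reading the protocol needs correcting before it is clear when the primary objective has been met. The difference between two-sided 0.05 in 7.3 and one-sided 2.5% in 7.2 plays no part, since both use 1.96.

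**What to change.** State once whether both tracers or at least one must succeed, and align section 1.4, the primary objective and hypothesis 1 in 7.1, the primary analysis in 7.2 and the sample size text in 7.3.

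- **If both:** keep the intersection-union test, write FDG- *and* FLT-PET in hypothesis 1, and restate power at N = 40 and AUC 0.75 as about 64–75% (planning formula) or 68–78% (DeLong), naming the correlation range. The cost is wording and a less favourable stated power. Keeping 80% instead would need about 45 to 53 evaluable patients by the planning formula (correlation 0.9 down to 0), above the recruitment maximum of 40 in section 3.2.
- **If either:** replace the intersection-union test with Holm at overall one-sided 2.5%, or a fixed testing order named in advance, and make the claim per tracer. Two unadjusted 2.5% tests would not do: at independence their familywise error is 1 − 0.975² = 4.9%. Holm has two costs. Power for one named tracer at the 1.25% step falls from 80% to about 71% (planning formula), or from 83% to about 75% (DeLong). And the simulated familywise error of DeLong with Holm at this sample size is slightly above nominal, about 3.2–3.3% at marker correlation 0.5.

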#### **3.2 Recruitment**

It is planned to recruit a maximum of 40 patients over a 15 months period.

Patients will be recruited after screening only if all inclusion criteria are met, no exclusion criteria are met and written informed consent has been obtained. No difference in recruitment concerning gender will be applied. According to the distribution of NSCLC more male than female study participants are expected.

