## Analysis of secondary endpoints

The prognostic value/accuracy of FDG/FLT-PET regarding clinical failure, SD and clinical response in NSCLC patients treated with erlotinib will be compared by ROC analysis; optimal cut-off values for FDG/FLT PET will be chosen (*secondary objective*).

Association between EGFR mutation, KRAS mutation and EGFR positivity with clinical response will be tested by Fisher's exact test.

Secondary endpoints (FFTF and OS) will be analyzed using descriptive statistics after at least one year follow-up of all patients.

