## 7.3 Further analyses

### Subsequent analyses

### Expected results

Based on the results of clinical trials with erlotinib in NSCLC patients in Western Europe and the US, we expect about 10% of patients with response (CR, PR) to treatment with erlotinib, about 30% with stable disease and about 60% with progressive disease. Furthermore, we expect about 90% of patients with mutated EGFR responding to therapy. KRAS mutations and EGFR mutations are expected to be nearly exclusive.

Based on published PET data, especially from patients with GIST treated with imatinib, we expect a nearly 100% association of clinical response (CR, PR in CT after 6 weeks of treatment) and reduction in SUV (PET analyses on days 8,9).

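### KRAS mutation is tested against clinical response (CR/PR), although the KRAS objective and hypothesis concern resistance and progression; at the planned rates the stated test has negligible power over most of the quoted KRAS range

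*Protocol*

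**What the plan says.** Section 7.2, under the analyses of primary endpoints, item 2, puts three markers against one outcome: "The statistical association of EGFR respectively KRAS mutational status, EGFR positivity and clinical response in NSCLC patients treated with erlotinib". The test is Fisher's exact test at one-sided 2.5%, with type 1 error control claimed if the PET test in item 1 is significant. The paragraph on secondary endpoints repeats the pairing: "Association between EGFR mutation, KRAS mutation and EGFR positivity with clinical response will be tested by Fisher's exact test".

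The aims in section 7.1 separate the markers. Secondary objective 5 reads "To confirm the statistical association of KRAS mutational status and clinical resistance to treatment of NSCLC patients with erlotinib". The second clinical hypothesis reads "EGFR mutations are found in patients with CR or PR and KRAS mutations in patients with PD after treatment with erlotinib".

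Clinical response is explained in section 7.3, Expected results, as CR or PR on CT after six weeks. The secondary-endpoint paragraph of 7.2 lists clinical failure, SD and clinical response as three separate outcomes.

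For planning, section 3.2 says "It is planned to recruit a maximum of 40 patients over a 15 months period", section 7.3 says "we expect about 10% of patients with response (CR, PR) to treatment with erlotinib", and the sample size assumptions give "10% responder, 60% progressers; thus 40% non-progressers". Section 1.3 quotes KRAS mutations in 15–50% of lung adenocarcinomas and uses about 15% as a working frequency.

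**The concern.** If KRAS mutation marks patients who progress, the contrast that shows it is PD against everyone else. A test against CR/PR pools SD with PD. It can then show the KRAS effect only as an absence of mutations among a handful of responders. With about four responders, having no mutated patient among them is unremarkable whatever KRAS does.

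The test also sits in the error-controlled sequence behind the PET test, so its result will look confirmatory. A non-significant result could be taken as evidence against KRAS-related resistance when the test had little ability to show it.

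**Working it through.** **The plan's own figure.** The only sample size in the protocol is for the AUC. With the binormal variance V = 0.0099·exp(−a²/2)·[(5a²+8) + (a²+8)/R], where a = 1.414·z(AUC) and R = 24/16 = 1.5:
- AUC 0.75: a = 0.954, V₁ = 0.116.
- AUC 0.50: a = 0, V₀ = 0.132.
- n = (1.96·√0.132 + 0.842·√0.116)² / 0.25² = 15.97, so 16 non-progressers and 24 progressers, 40 in total.
- Confidence interval half-width: 1.96·√(0.116/16) = 0.167.

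Both agree with the protocol (40 patients, 0.17). No sample size or power is given for the Fisher tests.

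**Inputs for the KRAS test.** N = 40; responders 10% = 4; PD 60% = 24, non-PD 16; one-sided level 0.025; KRAS-mutated 15–50% = 6 to 20 patients. I take the one-sided direction to be the hypothesised one, fewer mutations among responders.

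**Stated test, exactly 4 responders.** The most favourable table has no mutated responder. With k mutated patients the smallest p is C(40−k, 4)/C(40, 4), and C(40, 4) = 91,390.

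| KRAS-mutated | Smallest p |
|---|---|
| 6 (15%) | 46,376/91,390 = 0.507 |
| 10 (25%) | 27,405/91,390 = 0.300 |
| 20 (50%) | 4,845/91,390 = 0.053 |
| 23 (57.5%) | 2,380/91,390 = 0.026 |
| 24 (60%) | 1,820/91,390 = 0.020 |

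Significance first becomes possible at 24 mutated patients, outside the quoted range.

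**Test against PD, 24 PD.** The most favourable table has every mutated patient among the PD cases, and p = C(24, k)/C(40, k):
- k = 6: 134,596/3,838,380 = 0.035
- k = 7: 346,104/18,643,560 = 0.019
- k = 8: 735,471/76,904,685 = 0.0096

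**Power with random counts.** Outcomes are drawn at 10% response, 30% SD and 60% PD, and every mutated patient progresses:

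| KRAS frequency | Against CR/PR (stated) | Against PD |
|---|---|---|
| 15% | about 0% | about 35% |
| 20% | under 0.1% | 68% |
| 30% | about 1% | 98% |
| 50% | about 27% | 100% |

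If 90% of mutated patients progress, the PD test has about 15% power at 15% KRAS and about 32% at 20%. If 80% do, it has about 5% and 12%.

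**The case against.** **The wording may be loose.** Section 7.2 does not spell out the dichotomy, and the CR/PR gloss comes from a sentence about PET. Item 2 could be shorthand for the marker-specific pairs in hypothesis 2. Resistance could also be taken as mere non-response, which would make CR/PR the right outcome. Against this, 7.2 itself separates clinical failure, SD and response. Hypothesis 2 names PD. Section 1.3 sets the KRAS frequency against the PD rate when it discusses determinants of resistance. No sentence states a KRAS-versus-PD test. The mismatch stands on the text.

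**Objective 8 gives a KRAS–response analysis some basis.** It asks for EGFR and KRAS sequence features linked to response and SD. That is correct and is a reason to keep such a description, but it does not serve objective 5.

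**The test is not impossible.** A reader might infer from the 4-responder table that the KRAS objective can never be confirmed. The documents do not support that, because four is an expectation:
- At a 10% rate the chance of 5 or more responders among 40 is about 37%. With 5 responders and 20 mutated patients the smallest p is C(20, 5)/C(40, 5) = 0.024.
- The first-line cohort cited in section 1.2 had 13 responders among 53 (about 25%, or 10 of 40). With 10 responders, 11 mutated patients suffice (p = 0.024), although 6 do not (p = 0.155).

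The supported claim is negligible power over most of the range, not impossibility.

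**The remedy has limits.** The 15–50% range is for adenocarcinoma, whereas the trial enrols all NSCLC. At the protocol's figure of about 15%, the PD test with 6 mutated and 24 PD cannot reach 0.025 either. Its advantage also rests on hypothesis 2 being right. If mutations were spread evenly over SD and PD, simulated power at 50% KRAS would be about 27% for the stated test and 7% for the PD test.

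**Importance.** This is a secondary objective in an exploratory phase II trial sized for the AUC, and how a null result would be reported is a prediction. That limits the weight of the point without removing it.

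**Conclusion.** Wrong as written: the outcome fixed for the KRAS test in section 7.2 does not match secondary objective 5 or clinical hypothesis 2. At the planning rates the stated test has almost no power for that objective up to about 30% KRAS, and only about 27% at the top of the quoted range.

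These figures assume 40 evaluable patients, 10% response, the hypothesised direction and, for power, that every mutated patient progresses. Testing against PD matches the hypothesis and is much stronger from about 20% KRAS upward if nearly all mutated patients progress. It remains underpowered at about 15%. The point is worth correcting but does not touch the primary PET analysis.

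**What to change.** In section 7.2, in both item 2 of the primary-endpoint analyses and the secondary-endpoint paragraph:
- Keep EGFR mutation and EGFR positivity against CR/PR.
- Test KRAS mutation against PD versus non-PD (CR, PR, SD), one-sided for more PD in mutated patients.
- Keep KRAS by CR/PR and by SD as a descriptive analysis for objective 8.
- Report the PD proportion by KRAS status with exact confidence intervals.
- State that at about 15% KRAS the PD test is also underpowered (smallest p 0.035 with 6 mutated and 24 PD; power about 35% if all mutated patients progress, about 15% if 90% do), so the intervals rather than non-significance carry the conclusion.

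The cost is two amended sentences plus the reporting note. KRAS status and RECIST outcome are already collected, so no new data, patients or procedures are needed.

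### Three marker tests, each at one-sided 2.5% behind a single gate, do not give the strong type 1 error control the protocol claims

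*Protocol*

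**What the plan says.** Item 1 under Analyses of primary endpoints (Protocol 7.2) is the PET test, an "intersection-union test at one-sided level 2.5" per cent. Item 2 concerns the association between "EGFR respectively KRAS mutational status, EGFR positivity and clinical response in NSCLC patients treated with erlotinib", tested by Fisher's exact test, again at one-sided 2.5%, with the statement that "strong type 1 error control is maintained if analysis of item 1 was significant".

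The next subsection, Analysis of secondary endpoints, lists the same family again: "Association between EGFR mutation, KRAS mutation and EGFR positivity with clinical response will be tested by Fisher's exact test". It gives no level and no adjustment.

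Neither subsection ranks the three markers, divides the 2.5%, names a stepwise or closed procedure, or requires all three to succeed. The intersection-union rule is attached to item 1 only.

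**The concern.** Testing item 2 only after item 1 succeeds is a valid gate. It protects the step from item 1 to item 2. It does nothing among the hypotheses inside item 2 once the gate is open.

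Strong control must hold for every combination of true and false null hypotheses. One such combination is that PET does predict non-progression, so the gate opens, while no marker is related to outcome. There are then three chances of a false positive, each at the full level.

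Secondary objectives 4 and 5 (Protocol 3.1 and 7.1) are worded as confirmation of the EGFR and KRAS associations. As written, a single marker at p ≤ 0.025 could be reported as confirmed under strong error control, although the family has no such guarantee.

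**Working it through.** **Inputs**
- 40 patients; 10% responders and 60% progressers, so 4 and 24 (Protocol 7.3, Sample size calculation).
- Three tests, each at one-sided 2.5% (7.2).
- EGFR mutation 2–25%; KRAS mutation about 15%, or 15–50% in adenocarcinoma (1.3). EGFR and KRAS mutations are expected to be nearly exclusive (7.3, Expected results).
- The protocol gives no frequency of EGFR positivity; 12–32 of 40 is assumed in the grid below and 50% in the simulations.
- Directions follow Hypotheses, clinical (7.1): EGFR mutation with CR or PR, KRAS mutation with PD. EGFR positivity is tested against response.

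**The protocol's own figure.** The sample size states "Type-I-error 0.05; type-II-error 0.20". I used n = [z_α√V(0.5) + z_β√V(A)]²/(A − 0.5)², with V(A) = 0.0099·exp(−a²/2)·[(5a² + 8) + (a² + 8)/R], a = 1.414·z(A), R = 24/16 = 1.5. That this is the cited formula pair is an assumption. At A = 0.75 and two-sided 0.05:
- V(0.5) = 0.132 and V(0.75) = 0.116.
- n = (1.96 × 0.363 + 0.842 × 0.341)²/0.0625 = 15.97, so 16 + 24 = 40, as stated.

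One-sided 0.05 would give 33. The design level is therefore one-sided 2.5%, the level the family should respect.

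**Nominal familywise error with the gate passed**
- Independent tests: 1 − 0.975³ = 7.3%.
- Upper bound: 3 × 2.5% = 7.5%.

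**Attained error.** Fisher's test is discrete, so each test's true size is the hypergeometric probability of its rejection region. For a marker present in K of 40, tested against 4 responders, the denominator is C(40,4) = 91,390. Sizes are combined as 1 − Π(1 − size), treating the tests as independent.

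| EGFR-mutated / KRAS-mutated / EGFR-positive | EGFR mutation vs response | KRAS vs PD | EGFR positivity vs response | Combined |
|---|---|---|---|---|
| 6 / 8 / 20 | (20×34 + 15)/91,390 = 0.76% | C(24,8)/C(40,8) = 0.96% | 0 | 1.7% |
| 8 / 12 / 20 | (56×32 + 70)/91,390 = 2.04% | 0.76% | 0 | 2.8% |
| 3 / 19 / 16 | (3×666 + 37)/91,390 = 2.23% | 2.16% | 1,820/91,390 = 1.99% | 6.2% |

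With 20 EGFR-positive patients, even all 4 responders being positive gives p = 4,845/91,390 = 5.3%, so that test cannot reject.

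The grid runs over EGFR-mutated 1–10, KRAS-mutated 6–20 and EGFR-positive 12–32, which is 3,150 combinations. The maximum is 6.2%, the median 1.9%, and about 32% of combinations exceed 2.5%.

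**KRAS tested against response, as section 7.2 literally reads.** With 4 responders and 6–20 KRAS-mutated patients, the KRAS test cannot reject: at 20 mutated, no mutation among responders has p = C(20,4)/91,390 = 5.3%, and p is larger at lower counts. The two EGFR tests alone still reach 1 − (1 − 0.0223)(1 − 0.0199) = 4.2%.

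The first-line erlotinib study cited in section 1.2 had 13 responders among 53 patients, about 25%. With 10 responders and counts 8/11/29, the sizes are 1.45%, 2.36% and 2.36%, the last two both C(29,10)/C(40,10). They combine to 6.1%.

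**Averaged over random counts.** Simulations used 40,000 runs per scenario, EGFR and KRAS mutually exclusive, no marker related to outcome, all tests against response and the gate passed:
- 10% response: about 1.0–1.2%.
- 25% response, EGFR 25%, KRAS 30%: 2.6%.
- 40% response, EGFR 25%, KRAS 30–50%: 3.1%.

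**The case against.** The strongest reply is that discreteness makes the problem small in practice. At the expected 10% response and about 15% KRAS mutation (6 of 40), the KRAS test cannot reject: even if all six progress, p = 0.035. If 17 or more of 40 are EGFR-positive, that test cannot reject either. Only the EGFR-mutation test remains, with an attained size of at most 2.2% over 1–10 mutated patients. The 6.2% is a corner of the grid, needs 19 of 40 KRAS-mutated, and tests KRAS against PD although section 7.2 names clinical response. On that literal reading only about 7% of the grid exceeds 2.5%, with a maximum of 4.2%. The tests are also secondary, in an exploratory single-arm phase II trial, and the level is attached to item 2 as a whole, so an analysis plan might supply an order.

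Much of this stands as a limit on size: 7.5% should not be read as the actual error, and the expected inflation is modest. It does not rescue the claim. Strong control cannot depend on which marker counts turn up, and both readings of the KRAS endpoint exceed 2.5% for counts within the ranges examined. Testing KRAS against PD matches the clinical hypothesis in 7.1 and objective 5. An analysis plan may add a procedure, but the protocol already asserts the property without one.

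A fair point also concerns the repair: in a fixed sequence, a marker too rare to reach significance blocks those after it.

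**Conclusion.** The concern holds. The procedure in section 7.2 does not deliver the strong control it claims. The nominal familywise level is 7.3–7.5%. The attained level ranges from below 2.5% in many configurations to 6.2% in the worst case found at the protocol's 10/30/60 outcome mix.

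These figures take the gate as passed. The exact calculations treat the three tests as independent and all depend on an assumed frequency of EGFR positivity. The simulations do not assume that EGFR and KRAS mutations are independent, and they still exceed 2.5% at the higher response rates.

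The primary PET analysis is unaffected. The correction should be made because the statement is a positive claim that would support confirmatory wording for any one marker.

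**What to change.** Add one sentence to item 2 of section 7.2: after a significant item 1, test EGFR mutation, then KRAS mutation, then EGFR immunohistochemistry, each at one-sided 2.5%, stopping at the first non-significant result. The order follows secondary objectives 4 and 5, with immunohistochemistry last because no objective names it. Holm across the three is the alternative. Either makes the existing claim true. The same sentence should say whether KRAS is tested against response or progression.

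No patients or data are added. Under the fixed sequence, a later marker cannot be claimed if an earlier one fails. With 1 EGFR-mutated patient, or 6 KRAS-mutated, the test at that step cannot reach 2.5% with 4 responders and 24 progressers, so the sequence stops there. Holm avoids that blocking but starts at 0.025/3 = 0.0083. For example, 3 of 4 responders mutated among 8 EGFR-mutated patients (p = 0.0204) would not pass the first step. If neither cost is acceptable, withdraw the strong-control statement and label the three tests exploratory.
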